### Eligibility criteria {10}

The 1-month aortic computed tomography angiography (CTA) after open operation will be used to evaluate morphological characteristics, and the inclusion criteria are as follows: (1) patients aged 18 to 80 years old; (2) diagnosed with DeBakey type I aortic dissection within 90 days and 30 days after total arch replacement with frozen elephant trunk procedure; (3) no other aortic surgery history except total arch replacement with frozen elephant trunk implantation; (4) residual tear in the descending thoracic aorta; (5) the area of the FL at the level below the end of the frozen elephant trunk accounts more than 50% of the cross-sectional area of the aorta; (6) revascularization of the left subclavian artery; (7) life expectancy > 12 months; (8) patients can understand the purpose of the trial and voluntarily sign the informed consent form; (9) patients are able to complete follow-up according to the clinical trial.

The exclusion criteria are as follows: (1) pregnant or lactating women; (2) patients who are not suitable for endovascular repair, such as no appropriate vascular approach, allergy to alloy materials and contrast media, and severe renal insufficiency; (3) heritable aortic diseases or inflammatory aortitis.

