### Intervention description {11a}

Participants allocated to the experimental group will be admitted to the hospital promptly for the scheduled endovascular repair which will be performed by surgeons with at least 5 years’ experience. After the standard induction of general anesthesia, the invasive arterial blood pressure of the right radial artery will be monitored. Systemic heparinization (1 mg/kg) will be employed before the establishment of the common femoral artery access via which the endografts will be delivered. During the procedure, the end of the frozen elephant trunk will be used as the proximal landing zone, while the descending aorta above the diaphragm will be chosen as the distal landing zone. Endograft selection and coverage length will be largely left to the discretion of the operating surgeons based on imaging measurements. Patients in the experimental group will concurrently undergo conventional antihypertensive treatment as well.

Participants in the control group will not undergo early surgical treatment but will only receive routine antihypertensive therapy.

Follow-up appointments are scheduled at 3, 6, 12, 24, 36, 48, and 60 months after open surgery. An aortic CTA will be required for every follow-up.

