### Outcomes {12}

In this trial, the outcomes will be developed according to the standard clinical endpoint of endovascular aortic repair [17, 18]. The primary outcome will be the 5-year all-cause mortality. Secondary outcomes will include re-intervention (indications for re-intervention: aortic diameter ≥ 55 mm, aortic diameter growth rate > 10 mm/year, or pain or malperfusion symptoms [19]), aortic-related mortality, stroke, paraplegia, renal insufficiency, hepatic insufficiency, extremity ischemia, myocardial infarction, endoleak, graft infection, and graft migration. Other morphological outcomes will include segmental aortic remodeling and the FL thrombosis quotient.

The morphological measurements will be analyzed through three-dimensional reconstruction based on CTA images. The celiac trunk will divide the downstream aorta into two segments. Segment A will be from the end of the frozen elephant trunk to the celiac trunk, and segment B will be from the celiac trunk to the aortic bifurcation. The volume of FL, perfused false lumen (PFL), and true lumen (TL) will be measured for the two segments. The FL thrombosis quotient will be calculated using the formula FL_thrombosis quotient_ = 1-PFL/FL and given as a percentage, and the aortic remodeling will be classified into three types based on volumetric changes [20]. Positive aortic remodeling will be defined as a TL increase of > 10% with a stable FL or a FL decrease of > 10% with a stable TL. Changes within 10% will be considered stable, and all other conditions will be regarded as negative remodeling.

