## Statistical methods

### Statistical methods for primary and secondary outcomes {20a}

Baseline characteristics and clinical outcomes will be expressed as numbers (percentages) for categorical variables and mean ± standard deviation for continuous variables. The chi-square test or Fisher’s exact test will be used to analyze categorical variables, and the independent *t* test or the Wilcoxon signed-rank test will be adopted to analyze continuous variables. The Kaplan–Meier method will be performed to generate survival curves, and the log-rank analysis will be used to compare the differences between survival curves. Multivariate Cox regression adjusted by centers will be applied to calculate the hazard ratio risk. *P* < 0.05 will be considered to indicate statistical significance.

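### The tests named for the continuous CTA outcomes use neither the baseline scan nor the stratifying centre, and one of the two is a paired test

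*Protocol article*

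**What the plan says.** All references are to the protocol article.

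- **Test.** Under Statistical methods for primary and secondary outcomes {20a}, an independent t test or a Wilcoxon signed-rank test "will be adopted to analyze continuous variables". The only covariate adjustment stated there is for centre, in the Cox model.
- **Baseline scan.** Under Eligibility criteria {10}, "The 1-month aortic computed tomography angiography (CTA) after open operation will be used to evaluate morphological characteristics". Eligibility depends on this scan, so every randomised patient has it before allocation.
- **Follow-up scans.** Under Intervention description {11a}, "Follow-up appointments are scheduled at 3, 6, 12, 24, 36, 48, and 60 months after open surgery", and "An aortic CTA will be required for every follow-up".
- **Measurements.** Under Outcomes {12}, "The volume of FL, perfused false lumen (PFL), and true lumen (TL) will be measured for the two segments". The same section says "Other morphological outcomes will include segmental aortic remodeling and the FL thrombosis quotient". The quotient is 1 − PFL/FL, where PFL is the perfused false lumen, given as a percentage. The remodeling class has three categories, derived from volume changes.
- **Stratification.** Under Sequence generation {16a} and implementation {16c}, randomisation is stratified by centre.

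**The concern.** The design gives each patient a scan before randomisation and up to seven afterwards. Patients with a largely patent false lumen at one month may well differ later from those already partly thrombosed, whichever arm they are in. A t test on the follow-up value leaves that variation in the error term. It also leaves any chance baseline difference between two arms of about 70 in the estimate, and it omits the factor used to stratify randomisation.

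The alternative test is a separate error. The signed-rank test needs pairs, such as two readings on one patient. Offered as the alternative to an independent t test, it cannot be carried out between arms.

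At stake is how precisely the trial measures the effect of early endovascular repair on false-lumen thrombosis, which bears on the remodeling part of the aim under Objectives {7}.

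**Working it through.** **1. Arm size.** Sample size {14} gives 29.8% against 11.0% mortality, two-sided 5% and 80% power. The unpooled two-proportion formula is

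n = (1.960 + 0.842)² × (0.298 × 0.702 + 0.110 × 0.890) / 0.188² = 68.2, rounded up to 69 per arm.

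With 10% dropout, 69 / 0.9 = 76.7, rounded up to 77 per arm, or 154 in total. Both stated figures are reproduced, so 69 per arm is used below.

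**2. Unadjusted t test at one visit.** The difference detectable with 80% power, in standard deviations (SD), is (1.960 + 0.842) × √(2/69) = 0.477 SD.

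**3. With baseline adjustment.** If r is the correlation between baseline and follow-up, residual variance is multiplied by 1 − r². The detectable difference is then 0.477 × √(1 − r²), and the equivalent gain in patients is 1/(1 − r²) − 1. The documents do not give r, so 0.3 to 0.7 is assumed.

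| Assumed r | Variance factor | Detectable difference | Power at 0.477 SD | Equivalent extra patients |
|---|---|---|---|---|
| 0 (unadjusted) | 1.00 | 0.477 SD | 80.0% | none |
| 0.3 | 0.91 | 0.455 SD | 83.6% | 10% |
| 0.5 | 0.75 | 0.413 SD | 89.9% | 33% |
| 0.7 | 0.51 | 0.341 SD | 97.5% | 96% |

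**4. Late visits.** At the planning mortality, survivors at five years number about 69 × 0.890 = 61.4 and 69 × 0.702 = 48.4. The unadjusted detectable difference becomes 2.802 × √(1/61.4 + 1/48.4) = 0.54 SD. Adjustment shrinks it by the same proportion as in step 3. Missed scans would widen it further, and earlier visits would have fewer deaths.

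**5. The signed-rank test.** Allocation is parallel and 1:1 with no matching, so no patient in one arm has a partner in the other. The test could be applied to change within an arm, but that is not a comparison of arms.

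**The case against.** The strongest reply is that {20a} is one general sentence in a condensed article, and that covariates, the analysis visit and the repeated-measures structure are usually left to the analysis plan. As far as omissions go, that is right. But the sentence does more than omit: it names two tests. One is less efficient than the design allows, and the other does not fit the design.

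The sentence also does not say whether the t test applies to raw values or to change. A test on change would use the baseline scan. The text does not exclude it, but does not state it.

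Four stronger readings are tempting, and the document does not support them:

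- **That the t test is invalid or biased.** Under randomisation it is valid. The loss is in precision.
- **That the remodeling outcome ignores baseline.** The three-category class is built from volume changes and falls under the chi-square or Fisher test. The point concerns continuous measures only.
- **That many tests will be run.** Seven visits by two segments would give 14 tests of the quotient and, if they were independent, a 1 − 0.95¹⁴ = 51% chance of at least one false positive. With an assumed equal correlation of 0.5 to 0.9 it is about 35% to 14%. The article nowhere says that each visit will be tested, so these figures do not describe the plan.
- **That a mixed model would deal with deaths.** It would not. A model on available scans implicitly extrapolates values for patients who have died. Survivor selection affects the adjusted and unadjusted analyses alike.

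Two technical cautions also stand. The quotient is bounded, so a linear model is an approximation. And the procedure aims to change thrombosis, which could weaken the baseline correlation in the treated arm.

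**Conclusion.** The point holds as one of efficiency plus a wrongly named test. For the continuous CTA outcomes, the stated t test forgoes the baseline value and centre that the design supplies. The signed-rank test cannot make the comparison at all.

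The size of the loss rests entirely on the assumed correlation: a residual variance factor of 0.91 at r = 0.3 down to 0.51 at r = 0.7. If r were near zero there would be almost no gain, and the price of adjustment would be about four degrees of freedom, one for baseline and three for four centres.

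The importance is moderate. The article lists these measures after the secondary outcomes, and neither the sample size nor the primary mortality analysis depends on them. The change is worth making because it is cheap and the test name needs correcting in any case.

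**What to change.** 1. For each segment, analyse the FL thrombosis quotient at one named visit by ANCOVA with arm, baseline value from the eligibility CTA, and centre. Alternatively, use a repeated-measures mixed model with arm, visit, arm-by-visit, baseline, baseline-by-visit and centre, and take the contrast at that visit.
2. Report the other visits as estimates with confidence intervals. Treat the FL, PFL and TL volumes in the same way if they are compared between arms.
3. Replace the signed-rank test with the rank-sum test for any unadjusted comparison.
4. State that the adjusted estimate does not by itself resolve deaths before the named visit. Add a sensitivity analysis for them, for example a rank-based comparison that places death as the worst outcome. Such a comparison mixes survival with thrombosis and should be read that way.
5. Say how the quotient is scored when the false-lumen volume is zero, since the formula is then undefined.

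The cost is a change of wording, slightly more analysis work and a linear approximation for a bounded percentage. No new scans are needed, provided the baseline volumes are read from the eligibility CTA. Because the trial is unblinded, the change should be dated before anyone compares CTA results by arm. Recruitment is expected to end on 31 December 2023 with follow-up to 60 months, so on that schedule it can be made well before the final analysis.

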### Sample size {14}

The sample size is calculated based on the 5-year all-cause mortality. According to Roselli’s studies [21, 22], the all-cause mortality is estimated to be 11.0% in the experiment group and 29.8% in the control group. The calculation assumes two-side 5% type I error with 80% power. Therefore, we calculate that we demand 69 participants in each group. Considering the expected dropout rate of 10%, the final sample size is 154 for the entire study.

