## Assignment of interventions: allocation

### Sequence generation {16a} and implementation {16c}

The eligible participants will be divided randomly into experiment group and control group in a ratio of 1:1. Randomization will be stratified by centers in block sizes of 2, 4, 6, or 8. And an independent researcher will use SAS 9.3 (SAS Institute Inc., Cary, NC, USA) to generate the randomization sequence, ensuring an unbiased and reliable allocation process.

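### No single test is named to decide 5-year mortality, and centre, the randomisation stratum, is carried only into the Cox model

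*Protocol article*

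**What the plan says.** Outcomes {12} fixes the endpoint: "The primary outcome will be the 5-year all-cause mortality". The section on statistical methods for primary and secondary outcomes {20a} then gives three routes that could each test it:

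- chi-square or Fisher for categorical variables, in a paragraph that covers clinical outcomes as well as baseline data;
- Kaplan-Meier curves, where "the log-rank analysis will be used to compare the differences between survival curves";
- a regression model: "Multivariate Cox regression adjusted by centers will be applied to calculate the hazard ratio risk".

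One P<0.05 threshold follows all three, and no sentence ties the primary outcome to one of them.

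Other sections point in different directions. Sample size {14} works from two 5-year proportions: "all-cause mortality is estimated to be 11.0% in the experiment group and 29.8% in the control group". Section {20c} leaves patients with missing primary outcome data out of the primary analysis. Section {20b} runs the subgroup analyses of the primary outcome by adding an interaction term to the Cox model.

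On allocation, the sequence generation section {16a} states: "Randomization will be stratified by centers in block sizes of 2, 4, 6, or 8". In {20a}, centre appears only in the Cox sentence, and no strata are named for the log-rank test.

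**The concern.** The listed tests do not answer the same question. Chi-square and Fisher compare 5-year risks and need a known status at 5 years. The log-rank test and Cox model compare hazards and can use partial follow-up through censoring. The choice therefore affects who is analysed as well as the P value. With 10% dropout allowed for, 154 − 138 = 16 patients would be excluded under one reading and kept until censoring under the other. Only about 28 deaths are expected, so a result near the threshold is realistic. The trial is also open-label, which makes it more important that the decision rule is fixed in advance.

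Separately, when randomisation is stratified by centre, a test that leaves centre out tends to be conservative if mortality differs between centres, and so gives up power that the design could have kept.

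**Working it through.** **1. Reproduce the stated sample size.** Inputs from Sample size {14}: p1 = 0.110, p2 = 0.298, two-sided 5% error, 80% power, 10% dropout.

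- Two proportions, unpooled: n = (1.960 + 0.842)² × [0.110×0.890 + 0.298×0.702] / 0.188² = 68.2, so 69 per arm. The arcsine formula gives 68.5, also 69.
- Dropout: 69 / 0.9 = 76.7, so 77 per arm and 154 in total. Both stated figures reproduce.
- Other versions: pooled 71; continuity-corrected 82.
- Time-to-event formulas under proportional hazards: HR = ln(0.890)/ln(0.702) = 0.329. Schoenfeld needs 26 deaths, or 26/(2×0.204) ≈ 64 per arm. Freedman needs 31 deaths, or about 76 per arm. Neither gives 69.

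The trial was therefore sized on two proportions, although {20b} analyses the same outcome with Cox.

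**2. Power by test at 69 per arm.** Expected deaths: 69×0.110 + 69×0.298 = 7.6 + 20.6 = 28.2.

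- Chi-square without correction, exact enumeration: 80.2%.
- Fisher, exact enumeration: 74.3%. The two verdicts differ in 80.2 − 74.3 = 5.9% of trials.
- Log-rank, Schoenfeld approximation: 83.8%.
- Log-rank, simulated with exponential survival and complete 5-year follow-up: 80.0% without strata and 79.8% with centre strata (3,000 runs). A separate run of 15,000 trials gave 80.5% for both.

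In 4,000 simulated trials without loss, chi-square and log-rank disagreed in 1.5%. Chi-square, Fisher and log-rank were not unanimous in 6.9%.

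**3. Centre strata and choice of test.** Simulation of 138 patients in four centres, 3,000 runs per row. The centre sizes (69, 22, 22, 25) and the spread of centre hazards are assumptions, because the article gives neither. Monte Carlo standard error is about 0.7 points for power and 0.4 for type I error. The last column rejects if any of chi-square, log-rank without strata or centre-adjusted Cox is significant.

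| Log-hazard SD between centres | Power, log-rank without strata | Power, log-rank by centre | Type I, log-rank without strata | Type I, log-rank by centre | Type I, Cox | Type I, any of three |
|---|---|---|---|---|---|---|
| 0 | 80.0% | 79.8% | 5.7% | 5.8% | 5.4% | 6.1% |
| 0.5 | 73.8% | 76.8% | 3.4% | 4.0% | 3.9% | 4.3% |
| 1.0 | 67.8% | 80.3% | 2.6% | 5.2% | 5.0% | 5.2% |

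Power without strata falls down the table partly because this layout puts half the patients in the lowest-risk centre, which lowers the number of deaths. A further check at SD 1.0 gave a smaller gain, from 78.0% to 81.1%, with type I error rising from 2.9% to 4.4%. With no centre effect, 77 per arm and 10% loss, power was 81.6% without strata and 81.4% with them.

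Picking any of the three listed tests adds 0.7, 0.4 and 0.2 points of type I error over Cox alone. With 10% censoring and SD 0.5 the figures were 5.7% against 5.1%.

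**The case against.** This is a condensed article and its analysis plan is not shown. Which listed method carries the primary P value, and whether the log-rank test is stratified, are details that such a plan often settles. Kaplan-Meier, log-rank and Cox also form one familiar package, and the chi-square sentence is generic. That reading is reasonable, but it does not remove the problem. The sample size and the missing-outcome exclusion are stated in the article and fit a binary comparison, while the stated subgroup model is Cox. These sections have to be reconciled whatever a separate plan says.

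Four stronger readings are tempting and are not supported:

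- *The plan specifies an unstratified log-rank test and ignores centre.* It is silent on strata for that test, and it does adjust the Cox model for centre.
- *Choosing among the tests inflates type I error materially.* The tests are highly correlated, and the addition over Cox alone is under 1 point. The gap is larger against the log-rank without strata at SD 1.0 (5.2% against 2.6%), but only because that test is then conservative.
- *The trial may have only 74% power.* That is Fisher's figure. With 28 deaths in 138 patients, about 14 per arm on average, the usual small-cell reason for Fisher would not arise.
- *A log-rank test at 69 per arm has about 84% power.* That is the Schoenfeld approximation; simulation puts it near 80%.

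**Conclusion.** The point stands as one of specification. The article does not fix which test decides its only primary outcome, its own sections point both to a binary and to a survival analysis, and the randomisation stratum is written into only one of the listed methods. The stated sample size is not in dispute.

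The consequence is modest: under 1 point of type I error over Cox alone, and possible disagreement between tests close to P=0.05. A log-rank test without strata would be conservative, not invalid, if centres differ. The gain from stratifying is about 1 to 3 points of power for a log-hazard SD of 0.5 and 3 to 12 points for SD 1.0. Those ranges rest on assumed centre sizes and spread, exponential survival and proportional hazards. If centres do not differ, the cost is about 0.2 to 0.3 points.

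**What to change.** - In {20a}, name the log-rank test stratified by centre as the single primary test of all-cause mortality through 5 years.
- Give as estimates the hazard ratio from a centre-stratified (or centre-adjusted) Cox model and the Kaplan-Meier 5-year mortality difference with 95% CI.
- Label chi-square/Fisher on 5-year mortality as supportive.
- In {20c}, censor patients with incomplete follow-up at last contact instead of excluding them, so that the analysis set agrees with the primary test.
- In {14}, state that 69 per arm gives about 80% power for this test by simulation. N need not change.

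Age as a continuous covariate in the Cox model is an optional refinement; the article gives no figure for its benefit.

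The cost is wording plus, at most, the 0.2 to 0.3 points of power noted above. Recruitment was expected to end on 31 December 2023 and follow-up runs to 60 months after surgery, so at publication the rule could still be fixed well before the final 5-year data.

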### Data management {19}

Data will be collected in case report forms (CRF), including demographic characteristics, symptoms, signs, laboratory tests, medication, complications, and morphological outcomes. All the CRFs will be filled out independently by one researcher and checked by another researcher. All data collected during the study will be kept for 3 years after the completion of the study.

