### Methods for additional analyses (e.g., subgroup analyses) {20b}

Three prespecified subgroup analyses of age (18–49 vs. 50–80), gender and body mass index (< 24 vs. ≧ 24) will be conducted for the primary outcome by adding an interaction term (e.g., age × group) into the Cox regression model. A sensitivity analysis will be conducted for the primary outcome based on the per-protocol set, which included patients who adhered to the treatment and follow-ups.

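### The Cox model for 5-year mortality adjusts for centre only; adding baseline age would be a nearly free gain in precision, of modest size

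*Protocol article*

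**What the plan says.** Outcomes {12}: "The primary outcome will be the 5-year all-cause mortality". Statistical methods {20a} compares the survival curves with a log-rank test and, for the size of the effect, says "Multivariate Cox regression adjusted by centers will be applied to calculate the hazard ratio risk". Centre is also the only stratification factor in Sequence generation {16a}.

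Age appears elsewhere, but not as a covariate of that model:
- Eligibility criteria {10} admits "patients aged 18 to 80 years old".
- Data management {19} describes case report form content "including demographic characteristics, symptoms, signs, laboratory tests", so age is recorded.
- Methods for additional analyses {20b} makes age (18–49 v 50–80) one of three prespecified subgroup factors for the primary outcome, examined by "adding an interaction term (e.g., age × group) into the Cox regression model".

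Sample size {14} compares two crude proportions and assumes no gain from covariates: "the all-cause mortality is estimated to be 11.0% in the experiment group and 29.8% in the control group". No passage gives a figure for the effect of age on mortality.

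**The concern.** The endpoint is death from any cause over five years, in a population whose eligible ages span more than six decades. Age is a natural candidate for a strong baseline predictor, and the protocol treats it as important enough for a named subgroup. Yet it is neither balanced by the randomisation nor included in the model that yields the HR.

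With about 28 deaths, two things are at stake. A chance difference in age between the arms would feed into the reported HR of this one trial. Some precision that could be had without recruiting anyone would also go unused.

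**Working it through.** **1. The plan's own figure.** Inputs from Sample size {14}: mortality 11.0% and 29.8%, two-sided alpha 5%, power 80%. With the unpooled variance:

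n = (1.960 + 0.842)² × (0.11 × 0.89 + 0.298 × 0.702) / (0.298 − 0.110)² = 7.849 × 0.3071 / 0.03534 = 68.2, so 69 per arm.

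For dropout, 138 / 0.90 = 153.3, so 154. Both stated figures reproduce, with no role for age.

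**2. Deaths expected.** At 69 per arm: 69 × (0.110 + 0.298) = 28.2. At 77 per arm: 77 × 0.408 = 31.4. Under proportional hazards the implied HR is ln(0.89)/ln(0.702) = 0.329.

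**3. Power with and without age.** Assumption: HR per SD of age from 1.0 to 2.0. Simulation: 3,000 trials per setting, 69 per arm, exponential survival calibrated to 11.0% and 29.8%, normally distributed age, complete five-year follow-up, centre not modelled, Wald test of treatment.

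| HR per SD of age | Without age | With age | Change (points) |
|---|---|---|---|
| 1.0 | 79.3% | 79.2% | −0.1 |
| 1.3 | 78.6% | 79.7% | +1.1 |
| 1.5 | 78.1% | 78.7% | +0.6 |
| 1.7 | 78.5% | 80.1% | +1.6 |
| 2.0 | 79.7% | 83.1% | +3.4 |

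The Monte Carlo standard error of each power is about 0.7 points. Two further sets of runs with four centres agree. At HR per SD 1.5 they gave 78.0% v 79.5% and 77.3% v 78.8%. At 2.0 they gave 77.3% v 81.6% and 79.6% v 83.6%. Only at 2.5 is the gain large: 77.6% v 85.5% and 77.9% v 85.4%.

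**4. Validity.** With no treatment effect and an HR per SD of 1.7, type I error was 5.2% without age and 5.3% with it.

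**5. Effect of a chance imbalance.** The difference in mean age between arms has SD √(2/69) = 0.170 in units of the age SD. An imbalance at 1.96 times that is 0.334. The approximate shift in the HR is (HR per SD)^0.334:
- 1.3^0.334 = 1.09
- 1.7^0.334 = 1.19
- 2.0^0.334 = 1.26

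**6. Compared with the uncertainty already reported.** Deaths per arm are 69 × 0.110 = 7.6 and 69 × 0.298 = 20.6. SE(log HR) ≈ √(1/7.6 + 1/20.6) = 0.42, so the 95% confidence interval spans a factor of about exp(1.96 × 0.42) = 2.3 each way.

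**7. Parameters.** Treatment plus three centre indicators is four parameters, or 28.2/4 = 7.0 deaths each. Adding age to that model leaves 28.2/5 = 5.6. Treatment plus age with centre as strata is two parameters, or 28.2/2 = 14.1.

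**The case against.** The case for leaving the model alone is substantial. Adjusting for the stratification factor is a legitimate prespecified choice, and type I error is sound. The planned power does not depend on adjustment. The age effect is assumed, not documented, and at the weaker values the gain is close to simulation noise. Even the 1.26 factor is small beside an interval of 2.3 each way. An analysis plan that is not shown may add covariates. All of this stands, except that the last point is only partial: the article is not silent but states a model and names centre alone. The worry about few deaths per parameter is met by using strata.

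Four stronger readings are tempting, and the documents do not support them:
- **That the plan ignores age.** It does not: age is a prespecified subgroup factor for the primary outcome.
- **That chance imbalance biases the result.** Under randomisation it is random error, already in the confidence interval.
- **That the trial falls short of its stated power.** The 69 per arm reproduces without any covariate.
- **That the subgroup models omit main effects.** Read literally, adding only a product term to a model with treatment and centre would let ordinary age-related mortality pass as an interaction. Simulations at 77 per arm, with an even age split and centre omitted, gave false-positive rates of about 7% (HR 2 for older v younger) and 13% to 16% (HR 3), against 2% to 3% with the main effect. But the sentence is shorthand. It nowhere says that main effects are dropped, and an analyst would normally include them.

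**Conclusion.** The point holds as an efficiency improvement to a stated method, not as an error. The centre-only Cox model is valid but somewhat less efficient than one that also uses age.

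The size rests on the assumed prognostic strength of age. Power at 69 per arm changes by about 0 to 4 points for an HR per SD of 1.0 to 2.0, and more only if the effect is stronger still. A 2-SD chance imbalance would move the HR by a factor of about 1.09 to 1.26 for an HR per SD of 1.3 to 2.0. The power figures concern the Wald test from the Cox model, whereas the article names the log-rank test for comparing the curves, so they describe what the HR analysis gains and not a change in the log-rank result. The runs did not compare strata with centre indicators separately.

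**What to change.** In Statistical methods {20a}, prespecify that the HR for 5-year all-cause mortality comes from a Cox model with treatment and age as a continuous covariate, stratified by centre. Keep the log-rank comparison as planned. Fix this before database lock.

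In Methods for additional analyses {20b}, add that each interaction model also includes the main effect of the subgroup variable. This is a clarification only.

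The cost is one or two sentences, with no new data and no extra patients. Two small prices remain. The HR becomes conditional on age: at an assumed HR per SD of 2.0 the median simulated HR was 0.324 without age and 0.305 with it, so the report should say which is quoted. If age turns out not to predict death, almost nothing is lost (79.3% v 79.2%).
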